### 2.6. Outcome Measures

#### 2.6.1. Study Feasibility Outcomes

As the primary purpose of this clinical trial is to evaluate the feasibility of a large-scale herbal-medicine clinical trial for nonspecific chronic cough, the following eight feasibility outcomes will be assessed in consultation with specialists in respiratory medicine by referring to the Consolidated Standards of Reporting Trials statement for feasibility trials and similar studies [16,17,18]: (1) Recruitment rate of the clinical trial: the percentage of the number of enrolled participants to the total number of participants screened for eligibility during the clinical trial period; (2) Total participant recruitment period of the clinical trial: the time elapsed between the first and last participant’s screening visit (to estimate the recruitment period of the future confirmatory clinical trial); (3) The average number of enrolled participants per month during the clinical trial recruitment period; (4) Average compliance of participants with investigational products: the average percentage of individual participants’ actual use of investigational drugs during the clinical trial period as opposed to the intended use of those drugs; (5) Clinical trial adherence rate: the percentage of participants who take 70% or more of all investigational products compared to the total number of participants enrolled in the clinical trial; (6) Average cough diary record compliance of participants: the average percentage of the number of days in the cough diary actually logged by individual participants during the clinical trial period compared to the intended number of days; (7) Completion rate of clinical trial: the percentage of participants who complete the trial without dropout, including follow-up periods of 9 and 24 weeks, respectively, to the total number of enrolled participants in the clinical trial; and (8) Dropout rate of clinical trial: the percentage of participants who drop out before the end of the clinical trial to the total number of enrolled participants.

#### 2.6.2. Effectiveness Outcomes

The primary effectiveness outcome is the CSS score at Week 6. The CSS is a scale for the subjective assessment of cough severity and frequency that is reported by the patient during the daytime (08:00–20:00) and nighttime (20:00–08:00), and each subdomain of the scale is assigned 6 points, from 0 to 5. The total score is calculated as the sum of the daytime and nighttime scores (0–10 points) [19]. The validity and replicability of the Korean version of CSS have been verified [20]. Until Week 9, participants will be instructed to self-evaluate the CSS twice a day and record the score in a cough diary. During the telephonic follow-up survey (Week 24), participants will be asked to respond on their cough symptoms during the daytime and nighttime of the previous day. For statistical analysis, the average value (total, daytime, and nighttime scores) of the CSS since the previous visit that has been recorded in the cough diary and will be collected at each visit (excluding the baseline visit) will be used, and the average value of the previous 7 days will be used for determining the status at the baseline visit. The investigator will educate the participants on how to write a cough diary at every visit and attempt to minimize omissions in records. If less than 70% of the cough diary distributed at each visit has been completed, the participant will be dropped out.

The secondary outcome measures include the CSS (at weeks 3, 9, and 24), cough visual analog scale (VAS), the Leicester Cough Questionnaire (LCQ), the Hull Airway Reflux Questionnaire (HARQ), Integrative Medicine Outcome Scale (IMOS), Integrative Medicine Patient Satisfaction Scale (IMPSS), a five-level version of the EuroQol Five-dimensional Descriptive System (EQ-5D-5L), the EuroQol visual analog scale (EQ-VAS), yin deficiency score, and serum biomarkers.

For the cough VAS assessment, participants will self-evaluate their subjective discomfort based on cough severity, frequency, and urge to cough on a scale of 0 (no discomfort from coughing) to 100 (the highest discomfort imaginable) for the past 3 weeks [21]. This assessment will be undertaken at every visit, except for the screening visit, as well as during the telephonic follow-up survey (at Week 24), and will be investigated through a numerical rating scale (NRS) score from 0 to 100. The LCQ is a 19-item questionnaire designed to measure the quality of life of patients with cough and is divided into physical, mental, and social categories [22]. Each item is checked on a scale of 1 to 7, with higher scores indicating better health. The Korean version of the LCQ has been verified for validity and reliability [23]. The HARQ is a self-report questionnaire that measures cough hypersensitivity, and each of 14 questions is evaluated on a scale of 0 to 5. For normal individuals, the average score is 4 points, and the upper limit of the normal range is 13 points [24]. The IMOS is a tool for the investigator or participant to evaluate the degree of posttreatment improvement [25], and has been set as the investigator’s evaluation tool in this clinical trial. The IMPSS is an evaluation tool for ascertaining the participant’s treatment satisfaction [25]. Each tool is evaluated on a scale of 1–5 points. The EQ-5D-5L is a self-report questionnaire that is used to evaluate the quality of life, based on a 5-point scale over five areas: mobility, self-care, usual activities, pain/discomfort, and anxiety/depression [26]. The EQ-VAS asks participants to rate their own health from 0 (the worst imaginable health status) to 100 (the best imaginable health status) [26]. In case of telephonic follow-up (at Week 24), the EQ-VAS will be investigated through a 0 to 100 NRS. The Yin Deficiency Questionnaire is a pattern identification questionnaire with 27 questions, and the reliability and validity of this questionnaire have been established. Each question is evaluated on a 7-point Likert scale, of which points 1–4 are converted to 0 points and points 5–7 are converted to 1 point for calculation. The cutoff score for a yin deficiency diagnosis is 10 points [27]. The serum biomarkers include eosinophils, total immunoglobulin E (IgE), and plasma fibrinogen, which will be evaluated at the screening visit and at Week 6. In particular, during the telephonic follow-up survey (at Week 24), CSS, cough VAS, EQ-5D-5L/EQ-VAS, and cost questionnaires will be surveyed through a phone call.

#### 2.6.3. Safety Outcomes

To evaluate safety both before and after the administration of the investigational drugs, liver function (AST and ALT) and kidney function (blood urea nitrogen [BUN] and creatinine) tests will be conducted at the screening visit and at Week 6. In addition, the occurrence and frequency of adverse events will be evaluated at each visit through physical examination conducted by the investigator and through the participant’s self-report; moreover, the vital signs (blood pressure, pulse rate, and body temperature) will be measured at each visit and will be used as safety outcomes.

### 2.7. Sample-Size Calculation

This is the first exploratory clinical trial to evaluate the feasibility and preliminary effect of *Maekmundong-tang* administration in patients with nonspecific chronic cough. Therefore, there are no prior literature references for sample size calculation. Referring to a study that recommended a minimum of 12 people per group in a preliminary study in the field of life sciences [28], a total of 24 participants, with 12 participants per group, are needed. Considering a dropout rate of 20%, a total of 30 participants, 15 in each group, were specified as the target sample size.

### 2.8. Statistical Analysis

The statistical analysis of this clinical trial, in principle, will use full analysis set (FAS) analysis as the main analytical method; if necessary, a per protocol set (PPS) analysis will be additionally conducted. The FAS analysis group is defined as comprising participants with data measured for the outcome measures at least once after being randomly allocated, and all data obtained therefrom are included in the analysis. The PPS analysis comprises only participants included in the FAS analysis who have completed the entire process as specified in the protocol and have no significant violations that affect the trial results. The safety analysis includes all the data obtained from the participants who received the investigational product at least once. 

All statistical analysis is based on a two-sided test, and the significance level is set at 0.05. For continuous data, the mean and confidence interval are presented, whereas for categorical data, the frequency and percentage are presented. Statistics on the demographic and socioeconomic characteristics are presented for each group. Depending on normality, continuous data are analyzed using the independent *t*-test or Wilcoxon rank sum test, whereas categorical data are analyzed using the chi-square or Fisher’s exact test. For analyzing the effectiveness outcomes, the mixed-effect model repeated-measures method will be used, with each group and visit as the fixed factor and the participants as the random factor. If necessary, variables that show statistical differences in demographics or variables that can affect chronic cough will be set as fixed factors and analyzed. Intragroup differences in values before and after treatment will be analyzed, based on normality, with the Student’s paired *t*-test or Wilcoxon signed rank test. The IMOS and IMPSS scores are analyzed using Fisher’s exact test. The repeated-measures analysis of variance method is used to compare the difference in trend change between groups for the effectiveness outcomes, and Dunnett’s procedure is used for correction of the multiple-comparison analysis. If necessary, subgroup analysis will be performed by categorizing the participants according to their baseline characteristics (chronic cough pattern identification [29], presence of yin deficiency [27], sex, age, etc.). For the analysis of safety outcomes, the chi-square or Fisher’s exact test will be performed to compare the number of adverse events in the study groups. In addition, AST, ALT, BUN, creatinine, and vital signs will be analyzed using a paired *t*-test or Wilcoxon signed rank test to determine differences from before to after treatment. No interim analysis has been planned. All statistical analyses will be performed by a statistician, independently of trial procedure, by using the statistical program SAS^®^ Version 9.4 (SAS Institute Inc., Cary, NC, USA). 

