## 2. Methods

### 2.1. Study Design and Recruitment

A single-center, double-blind, randomized, active-controlled, parallel-group clinical trial will be conducted at the Daejeon Korean Medicine Hospital of Daejeon University in the Republic of Korea from February 2023 to December 2024. Only those individuals who voluntarily sign the written informed consent form to participate in the clinical trial after receiving a comprehensive explanation from the licensed Korean medicine doctors about the trial will be tested at the screening visit. Participants who satisfy the eligibility criteria will visit the hospital within 7 days to 3 weeks after the screening visit and will be randomly allocated to either the *Maekmundong-tang* group or the *Saengmaek-san* group in a 1:1 ratio. All groups will take investigational products for 6 weeks, and participants will visit the hospital every 3 weeks to undergo clinical evaluation. After taking the drug, a revisit will be performed 3 weeks later (week 9) to evaluate the effect and safety, and a telephone follow-up will be conducted at week 24 to conduct the economic evaluation (Table 1 and Figure 1). In summary, this study has a total of 6 visits (including 1 phone survey), and it will take approximately 6 months. To recruit participants, recruitment documents will be posted on hospital bulletin boards, websites, and applications. Additionally, subway, bus, and newspaper advertisements will also be implemented if recruitment is delayed. All trial processes will be conducted in accordance with the Declaration of Helsinki and Good Clinical Practice Guidelines. In particular, *Maekmundong-tang* has cough as an indication. In the Republic of Korea, a clinical trial is exempted from investigational new drug application if it targets a drug already approved by the Korean Ministry of Food and Drug Safety and is conducted within the scope of the indication permitted [14]. Therefore, pre-clinical data such as toxicity data are unnecessary for this type of clinical trial.

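### The per-protocol set has no Week 6 cut-off and no feasibility outcome reports Week 6 retention, although the primary effectiveness outcome is read at Week 6

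*Protocol article*

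**What the plan says.** - **Endpoint and timing.** Section 2.6.2: "The primary effectiveness outcome is the CSS score at Week 6". Section 2.1: "All groups will take investigational products for 6 weeks". Dosing and the primary effectiveness outcome therefore end together.
- **After Week 6.** There is a visit at Week 9, and "a telephone follow-up will be conducted at week 24 to conduct the economic evaluation". Section 2.1 includes this call among the trial's six visits, and Table 1 lists it as Visit 6.
- **Per-protocol set.** Section 2.8 admits only FAS participants "who have completed the entire process as specified in the protocol and have no significant violations that affect the trial results". It names no time point. The PPS analysis is additional to the FAS and is run only if necessary.
- **Feasibility outcomes (section 2.6.1).** Dropout, outcome (8), is "the percentage of participants who drop out before the end of the clinical trial to the total number of enrolled participants". Completion, outcome (7), counts those who "complete the trial without dropout, including follow-up periods of 9 and 24 weeks, respectively". Adherence, outcome (5), is "the percentage of participants who take 70% or more of all investigational products compared to the total number of participants enrolled".
- **Sample size (section 2.7).** Twelve per group are needed, then: "Considering a dropout rate of 20%, a total of 30 participants". The time point to which the 20% applies is not stated.

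**The concern.** A per-protocol analysis of a Week 6 outcome should select on conduct up to Week 6. Here, as written, membership also depends on the following 18 weeks, and several of the protocol's own rules can remove a participant in that time:

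- The diary continues to Week 9, and completing less than 70% of the diary given out at a visit means dropout (section 2.6.2).
- The list of treatments that lead to discontinuation applies throughout the trial period, with no stated end at Week 6 (section 2.5).
- Worsening cough is among the dropout reasons that section 2.9 anticipates.

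Some of these events may be related to treatment or to how cough behaves once dosing stops. Conditioning on them can bias the per-protocol comparison, and it discards valid Week 6 data.

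The feasibility side has a parallel gap. Section 2.6.1 makes feasibility of a larger trial the primary purpose. If that trial also has a Week 6 endpoint, it will need the proportion still evaluable at Week 6. The eight outcomes give attrition to the end of the trial and completion at Weeks 9 and 24, but not that figure.

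**Working it through.** **1. The plan's own figure.** The formula is N = n / (1 − d). With 24 evaluable and d = 0.20 (section 2.7), 24 / 0.80 = 30; per group, 12 / 0.80 = 15. Both match the protocol, so the stated sample size is not in error.

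**2. What happens to one participant.** Take someone with full dosing and diary to Week 6 who is lost at Week 12.

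| Place in the plan | Treatment of this participant |
|---|---|
| FAS mixed model (2.8) | Kept, with the Week 6 CSS |
| PPS (2.8), read plainly | Removed |
| Dropout, outcome (8) | Counted as a dropout |
| Completion, outcome (7) | Complete at Week 9, not at Week 24, if two rates are meant |
| Adherence, outcome (5) | Counted as adherent |
| Evaluable at Week 6 | Not reported by any outcome |

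**3. Size.** The protocol does not split losses into before and after Week 6, so two assumed readings of the 20% bracket the effect.

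*Reading A: the 20% is loss to Week 6.* Then 30 × 0.80 = 24 have Week 6 data. With a further loss L between Weeks 6 and 24, a whole-trial PPS is at most 24 × (1 − L):

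| Assumed L | PPS to Week 24 | PPS cut off at Week 6 |
|---|---|---|
| 5% | 22.8 | up to 24 |
| 10% | 21.6 | up to 24 |
| 15% | 20.4 | up to 24 |
| 20% | 19.2 | up to 24 |

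The PPS loses 24 − 22.8 = 1.2 to 24 − 19.2 = 4.8 participants who have Week 6 data.

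*Reading B: the 20% (6 of 30) is total loss to Week 24, of which k losses come after Week 6.* Week 6 loss is then (6 − k) / 30. For 100 evaluable in a later trial, the whole-trial rate gives 100 / 0.80 = 125. The Week 6 rate gives:

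| k late losses | Week 6 loss | Enrol, Week 6 rate | Excess from the whole-trial rate |
|---|---|---|---|
| 0 | 20% | 125 | 0% |
| 1 | 16.7% | 120 | 125/120: about 4% |
| 3 | 10% | 112 (111.1 rounded up) | 0.90/0.80 = 1.125: 12.5% before rounding |
| 6 | 0% | 100 | 125/100: 25% |

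**4. Could an existing outcome stand in?** Outcome (5) comes nearest, because less than 70% compliance at Week 6 is itself a dropout (section 2.5). It counts product taken, however, and a participant can reach 70% of product and still be dropped for an incomplete diary. Outcome (6) averages diary days and does not count evaluable people. Outcome (7) starts three weeks after the endpoint.

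**The case against.** The strongest reply is that the main analysis is untouched. A reader might infer that losses after treatment count against the primary Week 6 result. The documents do not support that: the FAS takes anyone measured at least once after allocation, uses all their data, and is analysed with a repeated-measures mixed model. The effect there is zero participants. The bias and wasted data concern only an optional supplementary analysis. This stands, and it limits the importance of the point.

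The Week 24 reading of the PPS is also an inference, since section 2.8 names no week and a fuller document may define it. That is fair. Even so, the wording refers to the whole process, and the protocol lists the telephone call as one of its visits. A rule that is already stated and reads this way deserves a cut-off.

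A reader might also infer that outcome (8) is wrong, or that it will be used to size the next trial. Neither is supported. Whole-trial dropout is a legitimate, clearly labelled figure, useful for a trial that collects costs and quality of life at Week 24. Nothing in the protocol ties it to a later sample size, nor ties the 20% allowance to Week 6. The planning error would arise only if someone used the figure that way.

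Finally, larger effects can be constructed. With 30% total loss, two thirds of it late, (1/0.70) / (1/0.90) = 1.286, an excess of 29%. But that assumes more dropout than the protocol allows for and is a single unfavourable case. The ranges above are the fairer statement.

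**Conclusion.** The point holds in a limited form. As worded, the PPS drops participants with valid Week 6 data because of later events, and the feasibility outcomes omit Week 6 retention, for which adherence is only a partial proxy. The main effectiveness analysis and the sample size of 30 are unaffected.

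The size rests on the unknown share of late losses. It is about 1 to 5 of 24 PPS participants under reading A, and 0 to 25% excess enrolment in a later trial under reading B. The second figure also requires that trial to have a Week 6 endpoint and its planner to use outcome (8) as the loss rate. The protocol gives no evidence on the direction of any bias in the PPS. This is a cheap improvement to make and does not threaten a planned result.

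**What to change.** 1. In section 2.8, define the PPS for Week 6 outcomes by dosing, diary completion and significant violations up to and including the Week 6 visit. Events after that visit should not affect membership. A separate PPS for every visit is not needed in a trial of 30.
2. In section 2.6.1, keep outcome (8) as it stands. Add the percentage of randomised participants with an evaluable CSS at Week 6, alongside Weeks 9 and 24, by arm. For Week 6, evaluable could use the protocol's existing 70% diary threshold over the interval since the Week 3 visit, because the Week 6 score is averaged over that interval.
3. State that the Week 6 figure is the one to use when sizing a confirmatory trial with a Week 6 endpoint.

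Visit and diary data are already collected, so no new procedures are required. The cost is a minor change of wording, which section 2.11 requires to be approved by the IRB and documented in the registry.

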### 2.4. Randomization and Blinding

The randomization sequence will be generated by block randomization method (mixing block sizes of two and four) without stratification. The allocation ratio for each group is 1:1. The randomization sequence will be generated using the statistical program SAS^®^ Version 9.4 (SAS Institute Inc., Cary, NC, USA) by a medical statistician, independent of the interventions and evaluations in this clinical trial. Participants who meet all the eligibility criteria will be allocated from the minimum available number to each group. 

In this clinical trial, all participants, investigators, and outcome assessors are blinded. Each participant’s group information according to the randomization order will be put in an opaque sealed envelope. It will not be disclosed until the end of the clinical trial, except when it is unavoidable to view group information due to the occurrence of a serious adverse event.

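### Baseline CSS is complete by entry rule but enters the effectiveness model only at discretion; fixing it as a covariate would remove 16 to 49% of the variance of a Week 6-only comparison if the baseline correlation is 0.4 to 0.7

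*Protocol article*

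**What the plan says.** All references are to the protocol article.

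- **Primary effectiveness outcome (section 2.6.2).** "The primary effectiveness outcome is the CSS score at Week 6". It is the mean of the diary scores since the previous visit.
- **Baseline value (section 2.6.2).** For CSS, "the average value of the previous 7 days will be used for determining the status at the baseline visit". Exclusion criterion 17 (section 2.3) turns away anyone without that 7-day diary, so the baseline value should exist for all who are randomised.
- **Allocation (section 2.4).** The sequence uses a "block randomization method (mixing block sizes of two and four) without stratification", so nothing in the design balances baseline cough severity.
- **Model (section 2.8).** "For analyzing the effectiveness outcomes, the mixed-effect model repeated-measures method will be used". The stated terms are fixed effects for group and visit and a random participant effect. A further sentence allows extra variables where judged necessary: those whose demographic comparison shows a statistical difference, or those thought capable of influencing chronic cough. No variable is named.
- **Size (section 2.7).** "a total of 24 participants, with 12 participants per group, are needed", raised to 30 for dropout.

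The article does not say whether Week 0 is one of the visits in the response, and it states no group-by-visit term for the mixed model.

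**The concern.** Baseline severity is usually among the best predictors of later severity on the same scale. Both CSS values here are averages over several diary days, which removes much of the day-to-day noise and makes at least a moderate correlation plausible. Leaving baseline CSS to a discretionary clause has three consequences:

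- If it is not used, the between-group estimate is less precise than the collected data allow.
- With 12 to 15 per arm and no stratification, a sizeable chance gap in baseline CSS is likely, and part of it passes into the Week 6 difference.
- A rule that depends partly on baseline tests works poorly at this size. Such tests miss many gaps large enough to matter, and the choice of model comes to depend on the data.

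The same applies to the other outcomes with a baseline value. What is at stake is the precision and credibility of the preliminary effect estimate. The feasibility outcomes are not affected.

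**Working it through.** **Inputs from the document.** Two-sided 0.05 (section 2.8); 12 per arm needed and 15 per arm targeted (section 2.7); 1:1 unstratified allocation (section 2.4).

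**The plan's own figure.** 24/(1 − 0.20) = 30, that is 15 per arm. It reproduces. The plan states no power, SD or effect size, so there is no power figure to check.

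**Assumptions.** The correlation r between baseline and Week 6 CSS is not given; I take 0.4 to 0.7. SDs are taken as equal at the two times, and differences are expressed in SD units.

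**Case A: Week 0 is not a response visit.** Relative to the Week 6 value alone, adjustment multiplies the variance by 1 − r², so the share removed is r². Estimating the slope costs a factor of 1 + 1/(2n − 4) for n per arm: 1 + 1/20 = 1.050 at n = 12 and 1 + 1/26 = 1.038 at n = 15. The net saving is 1 − (1 − r²)(1 + 1/(2n − 4)), and the equivalent size of 30 participants is 30/[(1 − r²) × 1.038].

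| r | Variance remaining, 1 − r² | Removed, r² | Net, N = 24 | Net, N = 30 | 30 act like |
|---|---|---|---|---|---|
| 0.4 | 0.84 | 16% | 12% | 13% | 34 |
| 0.5 | 0.75 | 25% | 21% | 22% | 39 |
| 0.6 | 0.64 | 36% | 33% | 34% | 45 |
| 0.7 | 0.51 | 49% | 46% | 47% | 57 |

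A simulation of 20,000 trials per setting gave savings of 12.0% and 13.3% at r = 0.4 (12 and 15 per arm), and 45.9% and 46.6% at r = 0.7, in line with the formula.

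The 95% half-width is t × SD × √[(2/n) × factor], with factor 1 and 2n − 2 degrees of freedom unadjusted, and factor (1 − r²)(1 + 1/(2n − 4)) and 2n − 3 degrees of freedom adjusted:

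- 15 per arm: 0.75 SD unadjusted; 0.70 SD at r = 0.4 and 0.55 SD at r = 0.7.
- 12 per arm: 0.85 SD unadjusted; 0.80 SD at r = 0.4 and 0.62 SD at r = 0.7.

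**Chance imbalance.** The difference in baseline means has standard error √(2/n): 0.37 SD at n = 15 and 0.41 SD at n = 12. Its 95% range (× 1.96) is ±0.72 and ±0.80 SD. Unadjusted, a gap moves the expected Week 6 difference by r times its size. At the edge of that range:

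- r = 0.4: 0.4 × 0.72 = 0.29 SD, or 0.4 × 0.80 = 0.32 SD.
- r = 0.7: 0.7 × 0.72 = 0.50 SD, or 0.7 × 0.80 = 0.56 SD.

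**Case B: Week 0 is a response visit and change from baseline is contrasted.** The variance relative to Week 6 alone is 2(1 − r): 1.20 at r = 0.4 and 0.60 at r = 0.7. Adjustment against this is (1 − r²)/[2(1 − r)] = (1 + r)/2, that is 0.70 and 0.85. The saving is 30% at r = 0.4, falling to 15% at r = 0.7, before the slope cost.

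**Case C: Week 0 is a response visit with baseline means constrained equal.** This uses the baseline about as efficiently as a covariate does, so the further saving is close to nil.

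**The case against.** Five points can be made against this.

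1. **Baseline CSS is not ruled out.** The clause on variables that may influence chronic cough is wide enough to admit it. This stands: a reader might infer that the plan excludes baseline CSS, but the text only leaves it unnamed and optional.
2. **The figures depend on an unstated model.** CSS is collected at Week 0 (Table 1), and section 2.8 also plans a repeated-measures analysis of variance to compare trends between groups. If Week 0 is a response, baseline is already used to some degree. This stands, and is why cases B and C are shown. A reader might treat 16 to 49% as the loss under any reading of the model, but the article does not fix the model well enough for that.
3. **The correlation is assumed.** No value is given, and the entry floor on CSS (exclusion criterion 18) narrows the baseline range and may lower r. This stands. Nor should the 0.51 at r = 0.7 be read as the loss: it is the share of variance that remains.
4. **A condensed article leaves covariates to the analysis plan.** This stands only in part. The article does not stay silent: it states the model terms and a rule for adding covariates, and it is that stated rule which is weak.
5. **The trial is about feasibility.** Section 2.6.1 makes this the primary purpose, and the sample size carries no power claim. This limits the weight of the point. It does not remove it, since a between-group effect estimate is planned and tested at 0.05.

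**Conclusion.** The point holds in a limited form. The plan states an effectiveness model in which the use of baseline CSS is discretionary and partly tied to baseline differences, although the value is complete by entry rule and allocation is unstratified.

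Its size rests on an assumed r of 0.4 to 0.7 and on how Week 0 is handled, which the article does not say. The full range in case A applies only if Week 0 is outside the response; under case B the saving is smaller except at low r, and under case C little is left to gain.

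A reader might go further and call the unadjusted comparison biased. The document does not support that: randomisation keeps it unbiased on average, and the harm is lost precision and exposure to a chance gap in this one small trial. The change should be made, because it costs almost nothing.

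**What to change.** - Prespecify the baseline value of each outcome as a continuous covariate, unconditionally. Alternatively, keep Week 0 as a response with the two baseline means constrained equal.
- State which of the two is used, and so whether Week 0 is in the response vector.
- Include a group-by-visit term, so that the Week 6 contrast is actually estimated and is not an average over visits.
- Remove covariate selection based on baseline tests. Name any further covariate in advance.
- Apply this at the post-baseline visits where each outcome is measured:
  - CSS, cough VAS, EQ-5D-5L and EQ-VAS: Weeks 3, 6, 9 and 24.
  - LCQ and HARQ: Weeks 3, 6 and 9.
  - Yin deficiency score and serum biomarkers: Week 6 only, by analysis of covariance, with the screening value as baseline for the biomarkers.

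IMOS and IMPSS have no Week 0 value and are not affected. Week 24 CSS is a telephone recall of the previous day, not a diary mean, which is a reason to let the baseline slope differ by visit.

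**Cost.** One parameter for a common slope, or up to four with a baseline-by-visit interaction over four visits. It is a change of wording and needs no new data.

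### The effectiveness model as listed (group and visit only) estimates an average difference over visits, whereas the primary effectiveness outcome is CSS at Week 6

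*Protocol article*

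**What the plan says.** Protocol article, section 2.6.2: "The primary effectiveness outcome is the CSS score at Week 6". The other CSS time points are secondary: "The secondary outcome measures include the CSS (at weeks 3, 9, and 24"). Baseline CSS is the diary mean over the 7 days before the baseline visit. Later diary values are means since the previous visit. Week 24 is a telephone report about the previous day.

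Section 2.8 gives the effectiveness outcomes a mixed-effect repeated-measures model, "with each group and visit as the fixed factor and the participants as the random factor". On covariates it says: "If necessary, variables that show statistical differences in demographics or variables that can affect chronic cough will be set as fixed factors and analyzed". It then adds a second longitudinal method: "The repeated-measures analysis of variance method is used to compare the difference in trend change between groups for the effectiveness outcomes". On multiplicity it says that "Dunnett’s procedure is used for correction of the multiple-comparison analysis".

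Sections 2.1 and 2.5 set 6 weeks of medication. Table 1 places CSS at Weeks 0, 3, 6, 9 and 24.

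**The concern.** The plan fixes a single primary time point and then lists model terms that do not isolate it. With only group and visit as fixed factors, the model has one group coefficient shared by all visits. That coefficient mixes Week 6 with Week 3 (mid-treatment), Week 9 (a diary mean over the first 3 weeks off drug) and Week 24 (18 weeks off drug, measured differently). If Week 0 counts as a visit, a difference that randomisation makes zero in expectation is averaged in as well.

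Baseline CSS is collected from everyone but is not named as a covariate. One of the two routes by which covariates may enter, a statistical difference in demographics, selects chance imbalances in a randomised trial.

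At stake is the preliminary effect estimate. Section 2.7 says there was no prior literature for the sample size, so this estimate is a natural input to the planning of a larger trial.

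**Working it through.** **The plan's own figure.** Section 2.7: 24/(1 − 0.20) = 30 in total and 12/(1 − 0.20) = 15 per group. This reproduces exactly, and nothing below changes it. It rests on a rule of thumb, with no effect size, SD or power.

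**What the listed model estimates.** In complete, balanced data the group coefficient of CSS on group + visit + random participant is

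group effect = (1/K) × Σ d_k,

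where d_k is the between-group difference at visit k and K is the number of modelled visits. A mixed model fitted to one simulated trial (15 per arm, 5 visits; assumed between-participant SD 1.2 and residual SD 0.9) gave a group coefficient of −0.484. The mean of the five visit differences was −0.484, and the Week 6 difference in the same data was −1.394. The identity needs no assumed effect size. With missing visits the average becomes a weighted one.

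**Size under assumed profiles.** The true Week 6 difference is set to −1.0. The profiles are assumptions.

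| Profile at Weeks 0/3/6/9/24 | Baseline as a visit (K = 5) | Post-baseline only (K = 4) |
|---|---|---|
| Week 6 only: 0/0/−1/0/0 | −1/5 = −0.20 | −1/4 = −0.25 |
| Rising, then waning: 0/−0.5/−1/−0.5/0 | −2/5 = −0.40 | −2/4 = −0.50 |
| From Week 6 on: 0/0/−1/−1/−1 | −3/5 = −0.60 | −3/4 = −0.75 |
| Constant from Week 3: 0/−1/−1/−1/−1 | −4/5 = −0.80 | −4/4 = −1.00 |

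Fits to large simulated samples (2,000 per arm) agreed with these values. Adding group-by-visit and reading the group difference at Week 6 gave −0.97 to −1.11 in every profile.

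**Precision at Week 6.** With 15 per arm and SD 1, the unadjusted SE is √(2/15) = 0.365. Adjusting for a baseline value with correlation ρ multiplies it by √(1 − ρ²):

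- ρ = 0.5: 0.866 × 0.365 = 0.316, a cut of about 13%.
- ρ = 0.7: 0.714 × 0.365 = 0.261, a cut of about 29%.

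The percentage cut is the same with the 12 per arm expected after dropout.

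**Precision of the averaged effect.** With four post-baseline visits and compound symmetry ρ, SE = √[(2/15)(1 + 3ρ)/4]. This is 0.289 at ρ = 0.5 and 0.321 at ρ = 0.7, smaller than 0.365. Whether averaging gains or loses power therefore depends on the profile:

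- A constant 1.0 SD effect gives the average 85% to 92% power, against 75% for the unadjusted Week 6 contrast.
- A profile of 0.5/1.0/0.5/0.2 SD at Weeks 3/6/9/24 averages 2.2/4 = 0.55 SD and gives 37% to 46%, against the same 75%.

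**Covariate route by significance.** The chance of at least one false difference among m independent variables tested at 5% is 1 − 0.95^m: 23% for m = 5 and 40% for m = 10. The protocol gives no list of variables, so m is an assumption.

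**The case against.** The strongest reply is that one condensed sentence in an article names the factors without excluding an interaction, and that a full protocol or SAP may supply the interaction, covariance and contrast. The planned test of trend between groups is itself a group-by-visit question, so the authors did not assume a constant effect. Part of this stands: it would be wrong to infer that the plan rules out an interaction. But the article chose to list its model terms, and the listed terms miss the named endpoint. The trend test is a separate test and gives no Week 6 estimate.

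Several stronger readings are tempting, and the document does not support them:

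- A reader might infer that covariates enter only through baseline significance. Section 2.8 also admits variables that can affect chronic cough, a route that could bring in baseline CSS. Its weakness is that it names no variable.
- A reader might infer that the estimate is always diluted and imprecise. With a constant post-baseline effect and baseline not modelled as a visit there is no dilution, and the average is then more precise than the unadjusted Week 6 contrast.
- A reader might infer that the repeated-measures ANOVA discards participants with a missing visit, or that Dunnett's procedure is misapplied to correlated visits. Both depend on implementation, which section 2.8 does not describe. Comparing several visits with baseline would be a many-to-one use. What can be said is that Dunnett's procedure adjusts nothing between two arms and that its scope is not stated.

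It is also fair that section 2.8 promises means and confidence intervals for continuous data, so Week 6 group means should be reportable whichever model is used.

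**Conclusion.** The mismatch stands. As listed, the model's group effect is an average over visits. It equals the Week 6 difference only if the effect is the same at every modelled visit and baseline is not a modelled visit. Treatment ends at Week 6 and two of the four post-baseline visits are off drug, so constancy cannot be presumed.

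The averaging result is algebraic. Its size is not known from the document: the ranges in the table come from four assumed profiles and are not bounds. The precision gain from baseline CSS rests on assumed correlations.

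The severity is moderate. A reader might take this as a flaw that invalidates the trial. The document does not support that, because section 2.6.1 makes feasibility the primary purpose, section 2.7 calls the trial exploratory, and no power was promised that could be lost.

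**What to change.** In section 2.8, state the effectiveness model as follows:

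- Outcome: post-baseline CSS at Weeks 3, 6, 9 and 24.
- Fixed effects: group, visit, group-by-visit, baseline CSS and baseline-by-visit.
- Within-participant covariance, with small-sample degrees of freedom.
- Primary effectiveness estimate: the Week 6 group difference with its 95% CI. Weeks 3, 9 and 24 are secondary contrasts.

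Week 24 may instead be analysed separately with baseline adjustment, because it is a one-day telephone report and not a diary mean.

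Replace the route that adds demographics found to differ statistically with prognostic covariates named in advance. The route for variables that can affect chronic cough may stay if those variables are named. Take the trend comparison from the same model, and state which comparisons Dunnett's procedure covers.

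The cost is wording plus a few model degrees of freedom. With four post-baseline visits the added fixed-effect parameters are 3 (group-by-visit) + 1 (baseline) + 3 (baseline-by-visit) = 7, or 2 + 1 + 2 = 5 if Week 24 is modelled separately. No new data are needed, and the target of 30 does not change.
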